##### Interviews and methods

Face-to-face interviews are organised with eligible participants identified from the screening stage after informed consent is granted. These interviews are conducted in a confidential environment in the participants’ homes or in a specific place set by study interviewers specifically trained for this purpose. Eligibility of the participant is first confirmed with the Washington Group questions: participants eligible as people with disability are asked additional questions from the extended Washington Group set (17 questions) to have more details on their functional limitation while controls are asked the same eight questions from the Washington Group questionnaire as part of the quality control.

After eligibility is confirmed, the full interview is proposed to the person. It includes a life-event interview on participants’ history of social participation, employment, resources, sexual partnership and fertility using the life-grid method.^43^
^62^ The life-grid is made of two A3 sheets divided into several columns (see online supplementary appendix B). The vertical axis represents the time; the first column gives time in years from birth to current year, the second column gives the age from 0 to current age and the third column gives the time elapsed. The other columns are used to report events according to their nature (people with whom the participant lived, main occupations/activities, resources, quality of life, sexual relationships, periods of transactional sex or sexual violence, pregnancies, children and disability onset). In addition, the occurrence of ‘important’ events is recorded as well as any information provided by the participants on the meaning of the events that occurred during his/her life. The life-grid helps to recall and structure the history of life events into chronological categories by cross-referencing the events. The grid is continually shown to the study participants as biographical information is recorded by the interviewer. The interview also includes closed questions on the participants’ characteristics, activity limitations, knowledge, attitudes and practices on HIV and SRH, environmental factors, social support and participation.

Several questions probing exposure to physical and/or sexual violence are asked at different moments of the interview. These questions are intended only to screen for violence and not to investigate the nature or circumstances of these events. However, the qualitative component of this study will aim to give a better insight into the exposure to violence. Where needed (eg, with deaf people or with people with intellectual disability), pictograms and other communication tools (like dolls, drawings and images) are used to facilitate communication between study interviewers and respondents. All interviewers received intensive training on study procedures, interview methods, as well as on disability and methods of communications with people with disabilities. Two interviewers are proficient in American and French sign languages and two have physical disability.

##### HIV testing

Each participant is offered voluntary HIV counselling and testing. It is carried out at the participant's home, or at any other place where there is assurance of confidentiality if the participant prefers. The counselling is led according to international guidelines. Communications strategies are adapted to each type of disability through the use of tools such as pictograms, dolls, drawings and wooden penis when relevant. Two rapid blood tests are used following national and international guidelines.^63^
^64^ HIV infection is initially screened using the sensitive rapid blood test Parallel Determine (Abbott, Japan) and further confirmed using the INSTI HIV-1/HIV-2 (bioLytical TM). An HIV ELISA antibody laboratory test will be performed in case of discordant results between the two rapid tests and for 10% of all tests as part of the quality control. All specimens are identified only through the anonymous study number to ensure confidentiality. For participants who refused HIV testing, a phone number is given for them to contact if they change their mind.

##### Statistical analysis

A weighted estimator will be used for prevalence and proportion estimates.^36^
^65^ CIs will be adjusted for the sampling design using the bootstrap method and the Rao and Scott corrected Pearson test will be used to compare proportions.

Potential risk factors for HIV will be identified using multilevel regression. Three categories of variables will be considered: individual characteristics, environmental characteristics and life-course characteristics. Multistate models will be used to analyse sequences of events and life transitions experienced. Social sequences from the life-course grid will be analysed using optimal matching algorithms.^66^ First, an overall analysis will be performed without accounting for the presence of a disability. This will provide a number of typical life trajectories. In the second step, the association between specific life trajectories and the presence of specific impairments and/or social participation restrictions will be assessed as well as the association between typical life trajectories and HIV vulnerability indicators. Univariate and multivariate logistic regression models will be used for these analyses.

### Exploratory work: results and study adaptation

Before starting the cross-sectional component, a mapping of the various organisations for people with disabilities was completed using a snowball method until saturation of the information. Additionally, a qualitative survey was implemented to assess the acceptability of the study procedures and determine possible barriers to reach people with disabilities. Using a purposive sampling method, a total of 10 semistructured individual interviews and 3 semistructured focus groups (each with 6 persons) were conducted. Focus groups were conducted separately with males and females. Interviews were carried out with people having visual, hearing and physical impairments, relatives of people with intellectual impairment and professionals working with people with disabilities. All interviews were audio recorded and transcribed. Transcripts were manually coded and analysed using thematic content analysis. All the interviewed persons with disabilities fulfilled the inclusion criteria of the HandiVIH study (age and activity limitations according to the Washington Group questionnaire). The exploratory interviews revealed five main themes that need to be considered in the implementation of the study. (1) Most of the key informants mentioned the frequent exposure of women with disabilities to physical and sexual violence. This was accounted for in the study implementation through the identification of referral organisations for victims of violence and specific training of the interviewers on that topic. (2) All key informants insisted on the importance of developing a trusting relationship during the interview with the person with a disability. The inclusion of people with disabilities in the interviewers’ team was a successful way to do that. The life-event interview also contributed to such a relationship. Besides, prior to launching the study, sensitisation sessions have been conducted in each enumeration area through media, reeves and traditional chiefs to increase the trust of families in the study. (3) Some key informants highlighted the fact that interviewers might need to be accompanied by another familiar person with a disability to gain the trust of some people with disabilities, a strategy that is used when necessary, and more often with persons living on the street. (4) Many key informants also stressed that people with intellectual disabilities may be hidden to the research team because of feelings of shame commonly found in their community. To overcome this issue, questions about the composition of the household are asked several times in different ways and at different periods of the enumeration and screening phases. In addition, interviewers have been trained and supported in developing interpersonal skills to get the trust of the first respondent of the household. (5) To finish, key informants explained that in Yaounde, since there is only one institution that can accommodate people with disabilities, most of them live in households. They also hold the view that most of the people with disabilities begging in the street belong to a household and only few of them actually sleep on the street.

The interview tools for the different phases of the survey were field-tested and adapted. Standardised reformulation of the Washington Group questions was prepared using the user and cognitive testing guidelines available from the website and from one of the co-authors (DM).

### Substudies: towards a better understanding of the disabled population throughout the spectrum

The backbone cross-sectional component might fail to include people with disabilities living on the streets. To address this concern, a substudy has been added that recruits beggars with disabilities through a purposive sampling strategy. After consent is granted, the same questionnaire and HIV counselling/testing as for the cross-sectional component participants are proposed to beggars with disabilities. In addition, information on their living conditions and on their social network is collected during the interview.

While most available studies recruit their study populations from DPOs’ networks, it has been pointed out that the characteristics of these populations may differ from those of the general population of people with disabilities who do not adhere to any groups or organisations. In the second substudy, members of the DPO mapped during the exploratory work are randomly recruited and offered to participate in the interviewing and to get an HIV testing/counselling after informed consent. Using the same statistical method as for the cross-sectional components, the characteristics of this subgroup will be compared with those of the participants in the main study to better understand to what extent data obtained from DPO members may reflect the situation of the overall population of people with disabilities.

For these two substudies, no formal sample size calculation has been performed because of their exploratory nature. However, a sample size of at least 50 participants in each sub-study was targeted in order to provide a power of 80% and to obtain results with a precision of at least 15%.

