### People with disabilities—a hard-to-survey population

People with disabilities living in resource-limited settings can be considered as a hard-to-survey population because of the technical challenges in identifying them,^34^ difficulty in establishing a sampling frame, and the existence of widespread exclusion mechanisms. Most studies available on HIV try to overcome such difficulties by using non-probabilistic sampling methods such as ‘snowball’ sampling.^35^ However, these methods do not allow for valid statistical inferences and lead to selection biases. One available alternative is a two-phase random sampling design with people with disabilities screened from the general population during the first phase and their eligibility confirmed during the second phase.^36^
^37^ However, particular attention needs to be paid to the screening questionnaire that should have acceptable sensitivity, specificity, validity and accuracy.^36^
^38^ This could be challenging in the context of disability. First, the wording of questions can create stigma and, as a result, people may be reluctant to identify themselves as disabled, or household members may experience shame at having a member with a disability and thus avoid identification.^39^ Second, the questions themselves may identify some disability types better than others. Third, the research communication process itself may be inaccessible for some groups of people with disabilities such as those with intellectual disabilities or the deaf-blind.

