##### Sample size

Sample size was computed to detect with a power of 80% and alpha risk at 5% a prevalence ratio >1.7 under the assumption that HIV prevalence in the controls is 6% in Yaoundé and that 10% of the participants may refuse the HIV test. A total of 850 persons with disabilities and 850 controls will be recruited. With this sample size, it is expected that each subgroup defined by impairments (hearing, visual, mobility, intellectual/mental) will include at least 100 participants. This is based on the assumption that the smallest subgroup will constitute at least 12% of the study population as it has been observed in other studies.^49^
^50^

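### The 80% power claimed for the 50-person substudies has no test, effect or alpha behind it, and neither power nor sampling precision can be claimed for the purposive one

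*Protocol article*

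**What the plan says.** The section on the substudies describes two exploratory samples.

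- The first "recruits beggars with disabilities through a purposive sampling strategy".
- The second recruits DPO members at random. For this one a comparison is announced: "the characteristics of this subgroup will be compared with those of the participants in the main study".

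On size, the section states that "no formal sample size calculation has been performed because of their exploratory nature". The next sentence says that "a sample size of at least 50 participants in each sub-study was targeted in order to provide a power of 80" per cent and "to obtain results with a precision of at least 15" per cent. Both properties are claimed for each substudy.

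Two other places bear on this. The main survey's Sample size section attaches its power to a prevalence ratio, a control prevalence and an error rate ("with a power of 80% and alpha risk at 5" per cent), and fixes the numbers: "A total of 850 persons with disabilities and 850 controls will be recruited". The background section on hard-to-survey populations says of non-probability sampling that "these methods do not allow for valid statistical inferences and lead to selection biases".

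**The concern.** Power is a property of a particular test against a particular alternative. The substudy section names no outcome, no difference and no alpha, and its previous sentence says that no formal calculation was made. The 80% therefore cannot be checked. The main survey's Sample size section shows that the authors state these inputs when a calculation exists.

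The two properties are also claimed for both substudies alike, although one is a purposive sample. That conflicts with the article's own position on what such samples can support.

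What is at stake is how the substudy results are read. The DPO comparison asks how far data from DPO members reflect the wider population of people with disabilities. A reader who trusts a printed 80% could take the absence of a significant difference as reassurance. Likewise, a precision figure for the sample of people begging would suggest a sampling basis that it does not have.

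**Working it through.** **Inputs from the article.** Substudy size n = 50 (a minimum); stated power 80%; stated precision 15%, with no confidence level and no indication whether it is a half-width; m = 850 main-study participants with disabilities; alpha 5%, given for the main survey only; HIV test refusal 10% and control prevalence 6% with ratio 1.7, also for the main survey only.

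**Assumptions.** The 15% is read as a 95% half-width in percentage points. For power, the article gives no effect, so three inputs are supplied here: a 15-point difference, the 850 as comparator, and a two-sided 5% test. Simple random sampling is assumed throughout.

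**Step 1: the precision figure.** Half-width = 1.96 × √(p(1−p)/n), largest at p = 0.5.

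- n = 50: 1.96 × √(0.25/50) = 0.139.
- n = 45 (if 10% refused the HIV test): 1.96 × √(0.25/45) = 0.146.
- Smallest n for ±15 points: 1.96² × 0.25/0.15² = 42.7, so 43.

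The exact (Clopper–Pearson) half-width at n = 50 is at most 14.5 points. The 15% therefore reproduces for a random sample of 50.

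**Step 2: the power figure.** It cannot be reproduced, because no effect is stated. As an illustration, let p0 be the main-study proportion, p1 = p0 + 0.15 the substudy proportion, and p̄ = (50·p1 + 850·p0)/900. Then

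power = Φ[(0.15 − 1.96·s0)/s1], with s0 = √(p̄(1−p̄)(1/50 + 1/850)) and s1 = √(p1(1−p1)/50 + p0(1−p0)/850).

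At p0 = 0.50: p̄ = 0.508, s0 = 0.0728, s1 = 0.0696, so (0.15 − 0.1426)/0.0696 = 0.106 and power = 54%.

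At p0 = 0.10: p̄ = 0.108, s0 = 0.0452, s1 = 0.0621, so (0.15 − 0.0886)/0.0621 = 0.988 and power = 84%.

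| Main-study proportion | Substudy proportion | Power, 50 vs 850 |
|---|---|---|
| 6% | 21% | 91% |
| 10% | 25% | 84% |
| 20% | 35% | 69% |
| 30% | 45% | 60% |
| 40% | 55% | 55% |
| 50% | 65% | 54% |

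Direction matters at low proportions: a fall from 20% to 5% has 87% power. Simulation of the same test gave 54.6% at 50% and 60.0% at 30%.

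**Step 3: other readings of the test.** For a 15-point rise from 30–50%, a one-sided 5% test against 850 gives 67–71%, a two-sided one-sample test 57–63%, and 50 against 50 gives 32–34%. None reaches 80%. At p = 0.5, a one-sample test at one-sided 10% does return n = 50 (50.1), but that is not the 5% the article uses.

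**Step 4: what 50 can detect.** Solving the Step 2 formula for 80% power gives a difference of about 14 points at p0 = 10%, 17.5 at 20%, 19 at 30%, and 20 at 40% and 50%. Detecting 15 points with 80% power at 30–50% would take about 86–95 substudy participants against 850.

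**Step 5: the purposive substudy.** Steps 1 to 4 need known selection probabilities. Purposive recruitment provides none, so these figures do not apply to the sample of people begging.

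**The case against.** The strongest reply is that the article never says that 15% is the difference to be detected; it attaches 15% to precision alone. The effect, the comparator and the sidedness used above are all supplied from outside the sentence. This stands. A reader might infer that the true power is 54–60% and that the authors miscalculated. The article does not support that: the power is undefined, and 54–60% is one illustration for common characteristics.

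A second reply is that the same reading meets 80% for uncommon characteristics. This also stands. For HIV itself, with 45 tested against 765 and a main-study prevalence of 10.2% (6% × 1.7), a 15-point rise has 80% power. The shortfall is confined to common characteristics.

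Third, the precision figure is right for the DPO sample. A reader might infer that it fails along with the power claim; Step 1 shows otherwise. A reader might also suspect that clustering by organisation would break it. The article does not say how members are drawn across organisations, and the methods it cites for the main survey already adjust for the sampling design, so this is not an error on the page.

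Fourth, both substudies are declared exploratory, 50 is a minimum, and the article nowhere says that a non-significant result will be read as similarity. This limits the severity. It does not justify printing a power figure that has no stated basis.

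**Conclusion.** The point holds in a limited form. The 80% power is unsupported: it follows a statement that no formal calculation was made, and nothing in the article says what it is the power to detect. On the assumed reading (15 points, 50 against 850, two-sided 5%, simple random sampling), 80% is reached at a main-study proportion of 10% (84%) but not at 30–50% (54–60%).

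The 15% precision is correct for the randomly recruited DPO sample under simple random sampling. For the substudy of people begging, neither figure can be claimed, on the article's own view of non-probability samples.

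The severity is minor. Both substudies are exploratory, and the main survey's comparison of HIV prevalence is untouched.

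**What to change.** - **Power:** delete the 80% claim, or replace it for the DPO substudy with detectable differences. For 50 against 850 at two-sided 5% and 80% power under simple random sampling, these are about 14 points for a proportion near 10% and 19–20 points at 30–50%.
- **Precision:** keep it for the DPO sample only, worded as a 95% half-width of up to about 14 points under simple random sampling.
- **Substudy of people begging:** report it descriptively, with no power or precision claim.

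The cost is a few sentences of wording, with no change to recruitment or data collection. The stated figures become less favourable for common characteristics.

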### Ethical issues

The final protocol has been approved by the ‘Comité d'Ethique pour la Recherche en Santé Humaine’ in Cameroon, and ‘Comité Consultatif de Déontologie et d'Ethique’ from the Institut de Recherche pour le Développement (IRD). Special attention has been paid to giving adapted information to persons with intellectual disabilities (using simple language and pictures) and involving them in the consenting process. Emphasis was also given to ensure confidentiality and privacy during the interview and HIV testing. Since some questions explore sensitive topics that may cause emotional distress, interviewers were trained to first provide psychological aid^67^ and to refer people requesting assistance to available services in Yaounde. All participants diagnosed with HIV infection received information about antiretroviral treatment and places where they could receive care. In addition, the study nurse proposes to those who are disabled to escort them at their first medical visit in order to decrease possible barriers.

## Discussion

To the best of our knowledge, this study will be one of the most comprehensive surveys on HIV and SRH to be conducted among people with disabilities in Sub-Saharan Africa. It will use a rigorous methodology to provide quantitative data on the burden of HIV among people with disabilities as well as information on their life situation.

In the cross-sectional component, the study attempts to overcome several methodological difficulties in identifying persons with disabilities that deserve attention. First, a relatively complex sampling design has been chosen to overcome the problem of identifying people with disabilities in the absence of a sampling frame, using a two-phase cluster random sampling with screening of disability at phase one. The rationale for this design is to use a first simple screening tool (here the Washington Group short set+2 questions) to reduce the population in which the more complex ‘diagnosis’ tool (here the Washington Group extended set) is used. Compared to snowball sampling that has been used in most available surveys, this sampling design decreases significantly the risk of selection bias. Available studies from Sub-Saharan Africa on the health of people with disabilities tend to rely on populations of people with disabilities identified from DPO or institutions (eg, schools) rather than from the general population. Data collected so far in the HandiVIH study confirm that the majority of people with disabilities recruited do not report connection to any known DPO, which suggests that populations of people with disabilities identified from DPOs may differ from the general population of people with disabilities. A trade-off had to be made between simplicity, ease, and speed of use of the screening tool and its sensitivity in order not to miss cases. In this study, it was decided to include two additional questions to the Washington Group short set to improve its sensitivity to detect intellectual or mental impairment because it was assumed that people with these impairments may be at an increased risk of sexual abuse and violence. The main potential limitation of this two-phase design is the inability of the screening tool (Washington Group questionnaire) to correctly partition the population into two groups defined by the disability status.

Various tools have been used to identify people with disabilities in the surveys and comprehensive discussions of their limitations have already been published.^13^
^26^
^34^
^68^ In this study, the two important features sought for the tool used to measure disability were its coherence with the ICF disability model and its ability to provide valid and reliable data that could be compared with similar data from other countries.

Currently, the Washington Group questionnaire is increasingly being used, recommended for use, and the most validated questionnaire for screening disability in adults.^69^ Although, to the best of our knowledge, it has not been used for HIV survey among persons with disabilities to date, the WG questionnaire has been used in other surveys on health,^70^
^71^ and is likely to be included in future Demographic Health Surveys ([name] personal communication). Nevertheless, this tool is based on the self-report of functional limitations and may not identify clinical impairments if the respondent does not consider his/her impairment as a limitation (so-called response shift in the field of quality of life assessment^72^
^73^). Two recent studies conducted in Cameroon and India have found that up to 46% of the people with disability identified through clinical impairment screening methods were missed by the Washington Group questionnaire.^74^
^75^ Another important issue is the determination of a cut-off in the level of difficulties that will differentiate people who are potentially with disabilities from those without. In this study, using the experience from two other surveys,^56^
^71^ it was decided that anyone with a major difficulty in at least one domain or some difficulties in at least two domains would be considered eligible as people with disabilities. To detect possible disability measurement errors done with the eight questions of the Washington Group questionnaire at the screening phase, disability eligibility is confirmed with the Washington Group extended set before enrolment in the second phase of the study. Lastly, it should be emphasised that the identification of functional limitations is only a first step to the identification of disability and needs to be complemented with additional questions on social participation and environment as well as impairment screening.^27^
^33^

An important feature of this research is the combination of different approaches to collect information on the study population. The quantitative cross-sectional survey constitutes the backbone of the project. However, since the population of people with disabilities is heterogeneous, complex and understudied, this quantitative component is completed with substudies having an emergent design. This heuristic approach is expected to give a more flexible and comprehensive understanding of the studied population while maintaining scientific rigour and quality. A first sub-study was defined to get a better understanding of the situation of the people with disabilities begging who may not have been included in the cross-sectional study. The second substudy, focusing on people with disabilities who are members of a DPO, is expected to provide more insight into possible limitations of epidemiological results based only on membership of DPO. These data are also expected to help to better adapt interventions to specific groups of people with disabilities (eg, beggars, members of DPO). As results accumulate, other qualitative researches connected to the project may be defined.

Another major challenge of this study is to get a better understanding of the mechanisms explaining the vulnerability of people with disabilities to HIV. It should be emphasised that the cross-sectional design of the study precludes any firm causal conclusion as could be done in a prospective cohort. However, the life-course approach used in the study may provide us with important information. The strength of the life-course approach lies in its ability to provide a comprehensive insight into the context, connecting sexual risk behaviour to other social factors and looking at events with an adequate time perspective.^76^ The life course perspective is particularly important in the context of people with disabilities who experience disadvantages that accumulate throughout the life.^77^ Besides, the life-grid method for collecting biographical information has been shown to improve the recall and thereby the accuracy of collected data.^44^ Retrospective data collection might not be as accurate as in prospective studies, although it was shown to provide information with good validity and reliability for some types of events.^78–80^ Moreover, the subjective assessment of events and life circumstances during the life-event interview is important information that may contribute to a better understanding of the life situation of people with disabilities and its relation to HIV risk. Interestingly, the life-event method gives more attention to the respondents’ perspective. Owing to this opportunity offered to respondents to account for their lives, the life-event method creates an environment conducive for sharing intimacy, which contributes to improving the quality and wealth of the data. It also gives the possibility to combine individual and social data. Although possible, the use of the life-grid method with people with intellectual disabilities is challenging. In our experience, a third person close to the respondent has to help in answering to the environmental activities and resource modules. Nevertheless, for most of this specific disabled population, the training of the interviewers as well as the use of the communication tools (pictograms, dolls) has allowed the collection of intimate data without the help of a third person, preventing the proxy bias in important topics such as sexuality and intimate relationships.

In conclusion, this study aims at providing comprehensive information on the vulnerability of people with disabilities to HIV and in their SRH. To address the multiple challenge of providing comprehensive and valid data on the vulnerability of people with disabilities to HIV and SRH adverse outcomes, an innovative approach is used, which needs to be shared and discussed with other stakeholders. The key aspects of this approach are (1) adoption of a disability-inclusive approach as much as possible; (2) use of an exploratory phase to adapt processes and tools to the specificities of the target population; (3) use of a random population-based sampling and of (4) standardised ICF-oriented questions to select people with disabilities in the study; (5) adaptation of the various tools to participants’ needs and (6) adoption of a life-course approach to better understand HIV and SRH vulnerability specifically related to disability. The findings of this research are expected to bridge important gaps in the knowledge and to inform decision-makers of the development of more accessible and appropriate HIV/SRH-related interventions for people with disabilities. They are also expected to stimulate additional research either to confirm these findings in other African settings or to broaden some aspects of the results.
